## Abstract

**Background:**

The use of Hartmann’s procedure in the old and frail and/or in patients with fecal incontinence is increasing, even though some data have reported high postoperative rates of pelvic abscesses. Abdominoperineal excision with intersphincteric dissection has been proposed as a better alternative and is performed increasingly both nationally and internationally. However, no studies have been performed to support this. The aim of this study is to randomize patients between Hartmann’s procedure and abdominoperineal excision with intersphincteric dissection and compare post-operative surgical morbidity and quality of life. The hypothesis is that intersphincteric abdominoperineal excision provides less pelvic and perineal morbidity.

**Methods/design:**

In this multicentre randomized controlled study, Hartmann’s procedure will be compared with intersphincteric abdominoperineal excision in patients with rectal cancer unsuitable for an anterior resection. The patients are operated in different ways around the ano-rectum, otherwise the same procedure is performed with total mesorectal excision and all will receive a colostomy. The one-month postoperative control will focus on post-operative surgical complications, especially the perineal-pelvic, reoperations and other interventions. After one year, late complications such as pain in the perineal or pelvic area or disorders such as secretion or bleeding from the anorectal stump will be recorded and a follow-up of quality of life performed. Histological and oncological data will also be recorded, the latter up to 5 years post-operatively.

**Discussion:**

The HAPIrect trial is the first randomized controlled trial comparing standard low Hartmann’s procedure with intersphincteric abdominoperineal excision in patients with rectal cancer with the aim of categorizing the post-operative surgical morbidity.

**Trial registration:**

ClinicalTrials.gov Identifier: NCT01995396. Date of registration November 25, 2013.

## Background

In patients with rectal cancer, low anterior resection (LAR) with total mesorectal excision (TME) is standard procedure [1]. Patients with rectal cancer are often elderly, many have comorbidities and some have a weak sphincter function with difficulties in keeping their stools. Anastomotic leakage after LAR is considered of multifactorial origin. Patients with co-morbidities like cardiovascular and/or pulmonary diseases (with impaired tissue perfusion and oxygenation) and therefore high ASA-class may be more prone to leakage. To reduce the risk of a life-threatening complication such as anastomotic leakage with fecal peritonitis, and/or to avoid crippling problems with fecal incontinence after LAR, a Hartmann’s procedure (HP) is sometimes performed [2]. In recent years, the proportion of rectal cancer patients, undergoing HP has increased from 10 to 15 % [3] and even more (30 %) in rectal cancer patients with metastases [4]. Many believe that HP is a safe operation, easy and quick to perform and associated with a low major complication rate and mortality [5–7]. It has been argued that the advantage of leaving a short ano-rectal stump, is that the patient experiences less problems with secretion and bleeding from the remaining rectum.

In recent years, there has arisen a debate in which some argue that the complication rate after HP is high, especially after leaving a very short rectal stump. A high frequency of pelvic abscesses, 12–33 %, are reported following a low HP, where the rectum is stapled off just above the pelvic floor [8–10]. Reasons for the high rate of pelvic complications in previous studies might be the selection of unfit patients with reduced vascular blood supply, even more pronounced after the low HP. The surgical technique, especially the transection of the rectum at the pelvic floor is probably also of importance. The broadest possible transverse stapler that fits into the pelvis in order to avoid tension in the stapler line (mostly 45 and 60 mm), has been proposed [7].

The alternative to a low HP would be to perform an abdominoperineal excision (APE) to avoid leaving a suture line on the rectum stump left in the pelvis, in order to reduce the risk of a suture line insufficiency which migth lead to a pelvic abscess. However, the problem with APE is that perineal necrosis and wound infections are common, with perineal wound problems ranging between 15 and 38 %, the latter after neoadjuvant radiotherapy [11]. This can probably be reduced to a large extent, especially after radiotherapy,by removing the anus with an intersphincteric dissection (ID), ie the muscular pelvic floor and external sphincter are left in situ. This means that one can seal the perineum with healthy muscle tissue, which improves healing as opposed to the traditional APE with sutures in the fatty tissue. Moreover, fat tissue suturing is often problematic as APE creates a large wound that is difficult to close, leaving blood/fluid cavities, which further increase the risk of infection. Intersphincteric proctectomy has been used for inflammatory bowel diseases such as Crohn’s disease and ulcerative colitis, and offers significantly less perineal defects than the traditional APE [12–14]. Whether an intersphincteric APE is better than HP in rectal cancer patients with regard to postoperative complications is unclear, although there are theoretical advantages. There are no published papers on the subject or on intersphincteric APE practised in rectal cancer patients, only a few abstracts that suggests low post-operative surgical complication rates after intersphincteric APE.

With regard to HP, there are no randomized studies or systematic reviews, only small case studies that have been analyzed retrospectively. In the few published studies of HP, the patients are often old with comorbidities, since HP is frequently the selected method for old or infirm patients. In the prevailing studies on HP, it has been compared with APE and/or anterior resection and data are not conclusive. The studies are heterogeneous and the study populations are not balanced. The patients that are preferably selected for HP, are very frail with high risk of post-operative complications and prolonged hospital stay. Therefore it is especially important to perform an operation that reduces the post-operative surgical complications as much as possible. A multicentre randomized study to identify the appropriate operative method for these old and frail patients with rectal cancer is warranted.

In this multicentre randomized study, we intend to compare the post-operative events after two surgical methods that can be used for rectal cancer in patients who are elderly, have other comorbidities or infirmities, and/or poor sphincter function, and thereby are not suited for a colo-anal/rectal anastomosis. The intention is to randomize patients between HP and APE with ID to investigate which method gives the lowest post-operative morbidity, and is associated with the best quality of life. The hypothesis is that an intersphincteric APE is superior to HP with regard to post-operative morbidity and quality of life.

## Methods/design

The HAPIrect trial is a multicentre, randomized study comparing Hartmann’s procedure with intersphincteric abdominoperineal excision in patients with rectal cancer.

Patients with resectable rectal cancer are randomized to either (A) a traditional Hartmann’s procedure or (B) abdominoperineal excision with ID of the anorectal stump. The patients are operated differently around the ano-rectum, otherwise the same procedure is performed.

Definitions: Rectal cancer: tumour border within 15 cm from the anal verge. Pelvic abscess: 1) pus-secretion via the anus and/or a clinical/endoscopic defect in the rectal suture line. 2) Computer tomography verified pelvic abscess.

### Primary endpoint

The primary objective of this trial is to observe the rate of local surgical complications (as graded by the Clavien-Dindo scale) within 30 days.

Secondary endpoints:Frequency of intra-operative rectal perforations.Duration of operation.Amount of blood loss.Re-operation and re-intervention (eg, percutaneous and transanal drainage) rate.Post-operative length of hospital stay.Re-admission frequency.Histology with TNM-status and resection margins.Local recurrence and metachronous distant metastasis rate.Survival after 3 and 5 years.Quality of life 1 year after surgery.Late local complications from the perineum or ano-rectal area within 1 year follow-up.

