### Registration protocol and collected data

Data on medical history, the medical work-up, laboratory data and operative data that are not collected in the SCRCR peroperative protocol, are recorded.

The following variables are recorded: age, sex, weight, height, ASA grade, WHO performance, dementia, symptoms, fecal incontinence, smoking, tumour location and height, TNM stage according to MRI, tethering of the tumour according to rectal exploration, presence of metastas, laboratory tests (albumin, CRP, WBC, Hb), previous radiotherapy, neo-adjuvant oncological treatment. Type of surgery, tumour location visavi peritoneal reflection, ligation of inferior mesenteric artery or not, skill level of the surgeon, width of bowel stapler (mm), make of surgical stapler, operation time, bleeding, associated peri-operative complications, ano-rectal stump divided or not in intersphincteric APE.

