### Randomization

The patients will be fully informed preoperatively orally and in writing and will have to sign an informed consent. We will explain pros and cons about the two types of operations and that we don’t know which one is the most appropriate and that we will make the randomisation during the operation. The patients are fully aware and have accepted this procedure if they are included in the study. This procedure was chosen to avoid bias in the selection of patients as regard the type of surgery. If you randomize before surgey then some surgeons could chose to not to include some patients because they want to perform one of the two types of surgery that they believe is easier, better or goes faster. This is the point, we don’t know which of the two types of surgery that is most appropriate for the patient because there exists no data or comparative studies. That’s why it is so important to randomisze during surgery to avoid this selection. Our Ethics committee in Uppsala have accepted this procedure.

The randomization procedure is performed in the operation theatre when the TME has been performed, the distal bowel tube has been clamped and a washout of the anorectum performed.

Randomization is performed per center by a central automated internet randomization module through the website ”www.norrlandskirurgi.se” and stratified for each centre. The website includes all necessary information and protocols.

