### Surgery

#### The operation, common to both surgical procedures

An experienced TME surgeon participates. The patient is stoma-marked pre-operatively by a trained nurse. Antibiotic prophylaxis, thrombosis prophylaxis, continuous thoracic epidural and laxatives are administered according to local practice. The patient is positioned with lowered leg supports.

The abdominal dissection is performed with a high or low ligation of the inferior mesenteric artery,dissection along the rectal mesentery, performing a total mesorectum excision down to the pelvic floor. A bowel clamp is applied below the tumour and the rectum is rinsed according to local practice. A suitable stapler is placed distally below the bowel clamp. The stapler is closed without fireing. The stapler is left in place. Now randomization is performed using the trial website. According to the results of the randomization (HP or APE with ID), the procedure is continued.

### Arm 1

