### Laparoscopic/robotic assisted surgery

Surgeons experienced in laparoscopic TME participates. Surgery is performed as in the open technique with TME dissection down to the levator. The rectum is closed distal to the tumour with a laparoscopic Satinský or an angled 45 mm stapler. Alternatively, the abdomen is opened with a Pfannenstiel incision above the pubic bone and the same clamping procedure as in open surgery is performed. After a rectal washout, the patient is randomized via the trial website, see above.

### ARM 1

If randomized to HA: transect the bowel with the laparoscopic stapler below the Satinský, or transect with cutting stapler below the non-cutting stapler - or alternatively transect through a Pfannelstiel incision and cut the bowel with knife above the stapler - and remove the specimen through an abdominal incision.

### ARM 2

If randomized to APE with ID, the bowel can be transsected with the laparoscopic stapler below the clamp, or transected with a cutting stapler below the non-cutting stapler –or alternatively transected through a Pfannelstiel incision and the specimen removed via the abdominal incision. ID is then performed as described above in the ARM 2 open procedure, with the patient in a lithotomy position. The anorectal specimen is taken out through the perineal wound.

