## Discussion

The HAPIrect trial is the first randomized controlled trial comparing standard low Hartmann’s procedure with intersphincteric abdominoperineal excision for rectal cancer. Patients with rectal cancer are increasingly old and many have other diseases and some have a weak sphincter function with fecal incontinence. HP has been increasingly used in the old and frail to reduce the risk of a life-threatening complication such as an anastomotic leakage with fecal peritonitis, and/or to avoid crippling problems with fecal incontinence after an anterior resection. To leave a short ano-rectal stump has been considered to cause less problems with secretion and bleeding from the remaining rectum. Especially in patients with metastases there has been an increase in performing a HP with the intention of avoiding severe post-operative surgical complications so that post-operative chemotherapy can be started as soon as possible [4]. During the last decade, there has been an ongoing discussion whether HP is a safe operation or not and high frequencies of pelvic abscesses have been reported (8). In the literature, only small observational studies that have been analyzed retrospectively can be found. Some authors found very high rates of pelvic abcsesses, especially after a low HP in up to 33 % of cases [10] compared with only 3 % in another paper [7]. There have been suggestions that an intesphincteric abdominoperineal excision is a safer procedure. No data on the use of intersphinteric excision in rectal cancer have been published but at least in two European centres efforts have been made to start a randomized trial but due to different reasons they have not been able to proceed. The advantage of intersphincteric APE would theoretically be that you avoid leaving a suture line on the rectum that can leak and cause a pelvic abscess. By removing the ano-rectal stump with an intersphincteric dissection, the perineo-pelvic defect is small and can be closed primarily by the levator muscles,thus favouring the healing. A disadvantage is the prolonged duration of surgery and the risk of perforation of the ano-rectal stump. A multicentre randomized study is necessary in order to provide evidence to support the theoretical advantages for intersphincteric abdominoperineal excision. The primary intention is to compare post-operative surgical morbidity between HP and APE with intersphincteric dissection. As secondary outcomes, the study will focus on re-operation and re-intervention, post-operative length of hospital stay, re-admission frequency, histological parameters, local recurrence, survival, late local complications and quality of life. The hypothesis is that intersphincteric APE provides less pelvic and perineal morbidity.

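### Operating time, blood loss and rectal perforation are listed as undivided totals although allocation happens only after the TME; splitting or adjusting at randomization would cheaply sharpen three secondary comparisons

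*Protocol article*

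**What the plan says.** All references are to the protocol article.

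- **Endpoints.** The list under Primary endpoint includes, as secondary endpoints, "Frequency of intra-operative rectal perforations.Duration of operation.Amount of blood loss". None has a stated start point, and the perforation item names no phase or site.
- **Time of allocation.** Under Randomization: "The randomization procedure is performed in the operation theatre when the TME has been performed, the distal bowel tube has been clamped", followed by a washout. For open surgery, the section on the operation common to both procedures has the stapler closed but not fired, then: "The stapler is left in place. Now randomization is performed using the trial website". For laparoscopic or robotic surgery: "After a rectal washout, the patient is randomized via the trial website, see above".
- **What differs by arm.** Methods/design: "The patients are operated differently around the ano-rectum, otherwise the same procedure is performed".
- **What is recorded.** Registration protocol and collected data lists "operation time, bleeding, associated peri-operative complications, ano-rectal stump divided or not in intersphincteric APE". Time and bleeding are single items, and no reading at randomization is listed.
- **Analysis.** Sample size considerations and statistics names a t-test or Mann-Whitney U test for continuous variables and states no adjustment. It names no test for perforation.
- **Expected harm.** Discussion, on intersphincteric APE: "A disadvantage is the prolonged duration of surgery and the risk of perforation of the ano-rectal stump".

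**The concern.** Allocation can affect only what happens after it. Everything up to the clamped and washed-out rectum is done before the arm is known, so time, blood loss and perforations from that phase are baseline data. As listed, they are pooled with the part of the operation that the arms can change.

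The stake is the trial's ability to see two harms that it expects itself: a longer operation and perforation of the anorectal stump. Both arise after allocation. In the Hartmann arm, little rectal work remains at that point beyond firing the stapler and removing the specimen. Many perforations counted in that arm could therefore come from the shared phase and make the arms look more alike. A non-significant result on the undivided count could then be taken as reassurance when it partly reflects dilution.

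Timing makes this a matter for the protocol and the operative form. Blood loss at randomization and the phase of a perforation must be noted in theatre. A later analysis plan cannot recover them if nobody wrote them down.

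**Working it through.** **The plan's own figure.** The only sample size given is for the primary endpoint: 35% versus 20%, alpha 0.05 (taken as two-sided), power 0.80.

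n = [1.96·√(2·0.275·0.725) + 0.842·√(0.35·0.65 + 0.20·0.80)]² / 0.15² ≈ 138 per group.

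This agrees with the stated 140, and nothing below changes it. The article gives no SD for time or blood loss and no perforation rate, so every input below is an assumption. n = 140 per arm is used throughout.

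**Duration: variance.** Let the SD be s₁ before and s₂ after randomization, with independent parts. The ratio of total to post-randomization variance is (s₁² + s₂²)/s₂².

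| s₁ (min) | s₂ (min) | Ratio | Information lost (1 − 1/ratio) |
|---|---|---|---|
| 30 | 40 | 2500/1600 = 1.56 | 36% |
| 30 | 30 | 1800/900 = 2.0 | 50% |
| 60 | 40 | 5200/1600 = 3.25 | 69% |
| 60 | 30 | 4500/900 = 5.0 | 80% |

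The same formula applies to blood loss, for which no plausible SDs can be taken from the article.

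**Duration: power.** Assume a true difference of 20 min and s₂ = 30. Power = Φ(20/(SD·√(2/140)) − 1.96).

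| s₁ | SD of the measure compared | Power |
|---|---|---|
| time from randomization only | 30 | above 0.99 |
| 30 | √(900 + 900) = 42.4 | 0.98 |
| 60 | √(3600 + 900) = 67.1 | 0.70 |
| 90 | √(8100 + 900) = 94.9 | 0.42 |

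**Perforation.** Assume 1% (Hartmann) versus 6% (APE) after randomization, and a common rate q before it. The counted rate in each arm is q + (1 − q)·p. For q = 5%: 0.05 + 0.95·0.01 = 5.95% and 0.05 + 0.95·0.06 = 10.7%.

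| q | Rates | Risk ratio | Risk difference (points) | Power |
|---|---|---|---|---|
| 0 | 1.0% vs 6.0% | 6.0 | 5.0 | 0.63 |
| 2% | 2.98% vs 7.88% | 2.6 | 4.9 | 0.44 |
| 5% | 5.95% vs 10.7% | 1.8 | 4.75 | 0.30 |
| 10% | 10.9% vs 15.4% | 1.4 | 4.5 | 0.20 |

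Power is from the normal approximation, which is rough at such low rates. The pattern matters more than the second decimal.

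**Check for bias.** With equal arms (2% after randomization in both) and a shared earlier rate of 5% or 10%, 100,000 simulated trials gave two-sided type I error of 0.046 and 0.049. For duration and blood loss, the expected pre-randomization part is the same in both arms and cancels from the mean difference.

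**The case against.** **The article is condensed.** Its endpoint list and variable list are each very short. Start points, the blood-loss method and the timing of perforations could be fixed in the full protocol or on the operative form. The whole-operation reading is indeed an inference from plain wording. But the variable list goes down to stapler width and make and still shows time and bleeding as single items, and nothing in the article points the other way. The improvement is worth making unless the form already has these fields.

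**Totals are legitimate outcomes.** The whole operation is what a frail patient undergoes, and the difference in mean total time estimates the same added minutes. This stands: totals should still be reported. It does not argue against adjustment, which targets the same mean difference with better precision.

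**Stronger readings.** A reader might infer that counting pre-allocation events biases the comparison. It does not: that phase is complete before allocation, type I error holds, and the perforation risk difference hardly moves. A reader might also infer that 70 to 80% of the information on duration is thrown away. That needs an earlier-phase SD of 60 min; at 30 min the loss is 36 to 50%, and power for a 20-minute difference is still 0.98 when s₂ is 30. Nor does the article say that the TME is the longest or bloodiest part of the operation.

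**Independence is assumed.** A positive correlation between the two parts would enlarge the variance ratio and a negative one would shrink it. This favours adjusting for the value at randomization over simple subtraction.

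**Conclusion.** The point holds as a cheap improvement of low to moderate importance, confined to three of the eleven listed secondary endpoints. As written, the comparisons are valid but less precise than they need be, and the perforation risk ratio is pulled toward 1. The size cannot be determined from the article. Under the assumptions shown, it runs from negligible (power 0.98 for a 20-minute difference with an earlier SD of 30 min) to substantial (0.42 with 90 min; perforation power falling from 0.63 to 0.20 at a shared rate of 10%).

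The case is strongest for perforation, because the Discussion names the anorectal stump specifically while the endpoint covers any intra-operative rectal perforation. The article does not support extending the point to the primary endpoint, the sample size or the validity of the trial.

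**What to change.** 1. **Operative form.** At randomization, and before the allocation is revealed, enter the clock time, cumulative blood loss and any perforation so far. Record the site of every perforation, whenever it occurs. The article does not say that the randomization website stores a time stamp, so the clock time should be a field on the form.
2. **Duration and blood loss.** Compare values from randomization onward, or compare totals adjusted for the value at randomization. The second option keeps the whole-operation outcome and the same mean difference.
3. **Perforation.** Make perforations after randomization, by site, the between-arm comparison. Report earlier ones by arm as baseline.
4. **Reporting.** Still give whole-operation time, total blood loss and all perforations.

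**Cost.** Three or four extra fields and one blood-loss reading during the operation. One weakness remains: a perforation made before randomization but noticed afterwards may be put in the wrong phase. Reporting the site and the overall count alongside lets readers judge how much that matters. Patients already operated on without these fields can contribute only totals.
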